### Randomization

Patient randomization is automatically done by using the electronic case report form software. A first randomization step allocates the study arms at the regional level: (i) six regions including patients in arms 1 and 2 (Aquitaine, Île-de-France, Lorraine, Nord-Pas-de-Calais, Rhône-Alpes, and Languedoc-Roussillon) and (ii) six other regions including patients in arms 1 and 3 (Alsace, Franche-Comté, Lower Normandy, Midi-Pyrénées, Pays de la Loire, and Provence-Alpes-Côte d'Azur). Then, within each region the patients are further randomized between the two groups (done at patients’ inclusion, between arms 1 and 2 or between arms 1 and 3). The distribution by center was 1:2 (ie, 1 patient of arm 1 for 2 patients of arms 2 or 3).

### Outcome Measures

The primary outcome measure of this study is to investigate the effect of a 12-month follow-up with the DIABEO system (software + physicians’ telemedicine, or software + nursing telemonitoring, and teleconsultations by diabetologist’s task delegation) versus usual follow-up in terms of improvement of glycemic control (HbA_1c_ levels) in T1DM or T2DM patients poorly controlled by a basal-bolus insulin regimen. HbA_1c_ high performance liquid chromatography assays are performed at qualified medical biology laboratories and then reported by participants to investigators. Secondary outcome measures are to compare groups for: HbA_1c_ levels, percent of responder patients (HbA_1c_ <7.5% or HbA_1c_ reduction ≥1%) and severe hypoglycemia at 6, 12 and 24 months, as well as for quality of life and satisfaction (of patients and physicians) at 12 and 24 months. Severe hypoglycemia was defined as requiring third-party assistance. Quality of life was assessed by a specific questionnaire, derived from the EuroQol five dimension scale (EQ-5D) questionnaire [11]. For participants of arms 2 and 3, satisfaction with the DIABEO telemedicine system is evaluated at each center, with a patient’s self-assessed specific questionnaire.

Other secondary, medico-economic outcome measures, have been designed to compare groups at 12 and 24 months for resource consumption and health insurance costs (including overall costs of diabetes and complications, and costs per point of HbA_1c_ reduction and for severe hypoglycemia avoided). If the study demonstrates an overall statistically significant effect, subgroups analyses will be conducted to identify the patients’ profiles with optimal costs consequences and cost-effectiveness ratios.

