### Study Design

TELESAGE is a randomized, open-label, three parallel-arms study that is to be conducted in approximately 100 public and private centers that employ diabetologists in France (Figure 1). The study protocol was designed by Centre d'Étude et de Recherche pour l'Intensification du Traitement du Diabète (CERITD; Evry, France). CERITD is a nonprofit clinical translational research center located in Corbeil Hospital (Corbeil-Essonnes, France). Selected centers have been already participating in the TELEDIAB 1 study [9]. Voluntis (Suresnes, France) provided the DIABEO software, Orange Telephone Company (Paris, France) provided the smartphone and telephone lines, and Sanofi (France) funded the study.

The study was designed to include a population of approximately 696 T1DM and T2DM patients poorly controlled with a basal-bolus insulin regimen (HbA_1c_≥8%) in real-life conditions. The patient recruitment period was estimated to last approximately 36 months.

The trial compares a control group (arm 1: usual follow-up) with the previously investigated DIABEO telemedicine service (arm 2: software + physician-assisted telemedicine as in the TELEDIAB 1 study [9]) or a new DIABEO telemedicine service (arm 3: software + telemonitoring and teleconsultations delegated by the diabetologists to a nursing staff) (Figure 1). Participants are asked to carry out at least two self-monitoring plasma glucose (SMPG) every day during the study. Patients randomized to arms 2 and 3 receive a smartphone with the DIABEO software. The investigator-physician fixes glycemic targets and associated treatment, alarm values, and values for self-adaptations. Patient enters daily three types of variables in the app: (i) SMPG levels before and after meals (6 measurements) + 1 optional in the night; (ii) carbohydrate counts; and (iii) planned physical activity. Patient entry data is automatically uploaded by the smartphone to a secured website (available to investigators at any time). If fasting or postprandial SMPG do not meet target levels, the system can suggest adjustments for carbohydrate ratio, long-acting insulin analog dose, or pump basal rates.

Following a screening period of 10 days, the main study period will last 12 months, with an optional extension period of at least 12 additional months (Figure 1). If desired, patients from the control group can begin to use the software after 12 months.

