**Figure 2 figure2:**
[figure not shown]
Road map of arm 3. Patient enters daily three types of variables in the DIABEO application (step 3): (i) Self-measured plasma glucose levels before and after meals (6 measurements) + 1 optional in the night; (ii) carbohydrate counts; and (iii) planned physical activity (see text for other technical details). HCP: health care practitioner.

**Table 1 table1:** Clinical study flow diagram; schedule of enrollment, interventions and assessments. EQ-5D: EuroQol five dimension scale; HbA_1c_: glycated hemoglobin.

Conponents	Visit #1	Visit #2	Visit #3	Visit #4^a,b,c^	Visit #5^d^ (Optional extension)
Evaluations	Day 0	Month 6	Month 12	Month 24	End of study
Informed consent	✓		✓^e^	✓^d^	
Inclusion / exclusion criteria	✓				
Medical history	✓				
Demographics	✓				
Concomitant treatments	✓	✓	✓	✓	✓
Clinical examination	✓	✓	✓	✓^a,f^	
Randomization	✓				
Weight	✓	✓	✓	✓	✓
Blood pressure	✓	✓	✓	✓^a,f^	
Last HbA_1c_ values	✓	✓	✓	✓	✓
Questionnaires (EQ-5D)	✓		✓	✓^a,f^	
DIABEO initiation	✓^a,b,f^		✓^c^		
Nursing appointment^a^	✓		✓^e^		
Fixing appointment for visit #3		✓			
Satisfaction questionnaire “DIABEO”			✓^a,f^	✓^a,f^	
Severe hypoglycemia		✓	✓	✓^a,f^	
Symptomatic hypoglycemia (≤15 days before)			✓		
Adverse events	To be reported all throughout the study				
Serious adverse events	To be declared to sponsor within 24 hours (next business day)				
Malfunction of the DIABEO software^f^	To be reported all throughout the study				
Care consumption	To be reported every month by all concerned patients				
Remittance of TELESAGE books	✓		✓^a,f^		

^a^Applicable to group 3 (software + nurses’ telemonitoring and teleconsultations).

^b^Initiation takes place within approximately 10 days after the inclusion visit.

^c^Applicable to patients of group 1 (control) continuing the study after 12 months and using the software.

^d^Applicable to patients wishing to use DIABEO during the extension phase and who have not yet signed a consent for that purpose.

^e^Applicable to patients of group 1 (control) continuing the study after 12 months and using the software + nurses’ telemonitoring and teleconsultations.

^f^Applicable to group 2 (software + physicians’ telemedicine).

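### Group comparisons are planned at 24 months, but no protected usual-care control is guaranteed after month 12, and Table 1 schedules month-24 severe hypoglycaemia and EQ-5D only for the two DIABEO arms

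*Protocol article*

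**What the plan says.** The primary outcome (Methods, Outcome Measures) is the HbA1c effect of DIABEO against usual follow-up at 12 months. The same section lists secondary comparisons between groups that run later: HbA1c, responders, "severe hypoglycemia at 6, 12 and 24 months, as well as for quality of life and satisfaction", the last two at 12 and 24 months. The medico-economic outcomes are "designed to compare groups at 12 and 24 months for resource consumption and health insurance costs", and they include a cost per severe hypoglycaemic event avoided.

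Study Design describes a 12-month main period "with an optional extension period of at least 12 additional months", and adds: "If desired, patients from the control group can begin to use the software after 12 months".

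In Table 1, the row "Severe hypoglycemia" has unrestricted ticks at months 6 and 12, and the EQ-5D row has them at day 0 and month 12. In both rows the month-24 tick carries notes a and f, which stand for groups 3 and 2. The month-24 HbA1c tick has no arm note. The Visit 4 column header carries notes a, b and c, and note c reads "Applicable to patients of group 1 (control) continuing the study after 12 months and using the software".

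The Data Analysis section has efficacy outcomes analysed by intention to treat and does not distinguish month 24 from month 12.

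**The concern.** A secondary comparison at 24 months, listed beside the 12-month one with no change of description, will be read as the same question asked later: DIABEO against usual care. After month 12 the design no longer protects that contrast. Continuation is a choice, and so is a control's uptake of the software.

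Three things are at stake. A small or null difference at month 24 could be taken for loss of effect when it reflects controls having started DIABEO. A 24-month cost-effectiveness ratio could carry a usual-care label although part of its comparator uses the product. And for severe hypoglycaemia and EQ-5D, the article promises a comparison for which its own schedule sets no control assessment. The economic side matters because the Introduction names cost reduction to the health insurance system as something the trial will assess, and says that renewal of the device's approval depends on this study's results.

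**Working it through.** The plan gives no figure to reproduce here. The check is a comparison of sections, followed by an illustration.

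**Step 1. Month-24 comparison against month-24 control data, outcome by outcome.**

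| Outcome compared at month 24 (Outcome Measures) | Control-arm data at month 24 (Table 1) |
|---|---|
| Severe hypoglycaemia | Tick limited to groups 2 and 3; general adverse-event reporting is unrestricted |
| Quality of life (EQ-5D) | Tick limited to groups 2 and 3 |
| HbA1c, and responders derived from it | Tick without arm restriction |
| Resource use and costs | Monthly care-consumption report, not limited to groups 2 and 3 |
| Cost per severe hypoglycaemia avoided | Needs a control event count; no dedicated month-24 entry |
| Satisfaction with DIABEO | Groups 2 and 3 by design; no control needed |

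Rows 1, 2 and 5 conflict with the outcome list. Because the earlier ticks for rows 1 and 2 carry no note, the month-24 restriction looks deliberate.

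**Step 2. Who the month-24 controls are.** Where control data can exist (HbA1c, responders, costs), they come from patients who chose to continue. Some will have started DIABEO and some not, again by choice. By randomised group, the contrast is early against optional delayed start.

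**Step 3. Size of the dilution, as an illustration.** Let x be the share of month-24 controls who have switched. The article gives no value for x. Assume that the 0.5-point difference used in Patient Population Size persists to month 24 and that switchers gain all of it. Then:

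expected contrast = 0.5 × (1 − x)

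For power, take the SD of 1.2, 15% not evaluable and intracluster correlation of 0.005 from Patient Population Size. With 696 patients in 12 regions, 696/12 = 58 per region, so the design effect is 1 + 57 × 0.005 = 1.285. Two-sided alpha of 0.05 is an assumption. Assuming an equal split between the two sets of regions and 1:2 allocation, 348 patients per set gives 116 controls and 232 in one DIABEO arm; pooled, 232 and 464.

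Effective controls = 116 × 0.85/1.285 = 76.7, with twice that number treated. SE = 1.2 × √(1/76.7 + 1/153.5) = 0.168. Power = Φ(contrast/SE − 1.96). For the pooled comparison, SE = 0.119.

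| x | Contrast (HbA1c points) | Power, one DIABEO arm | Power, pooled |
|---|---|---|---|
| 0% | 0.5 | 85% | 99% |
| 25% | 0.375 | 61% | 88% |
| 50% | 0.25 | 32% | 56% |
| 75% | 0.125 | 11% | 18% |
| 100% | 0 | 2.5% | 2.5% |

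The formula counts rejections in favour of DIABEO only, hence 2.5% in the last row. Loss of patients who decline the extension is not included and would lower these figures. A smaller benefit in switchers would raise them.

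**The case against.** The strongest reply is that the problem is narrower than it may look. A reader might infer from the Visit 4 header that no unexposed control exists at month 24 for any outcome, or that nearly every control seen then has switched, since note c names only controls who use the software. The document does not support that:

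- Uptake by controls is optional, and no rate is stated.
- The month-24 HbA1c tick is unrestricted, and the Clinical Study Flow Diagram section lists visit 4 among the HbA1c measurements without naming arms.
- The header is not a dependable list of attendees. Read literally it omits group 2, which the cell notes include, and its note b concerns initiation about 10 days after inclusion.
- The month-24 consent tick carries note d, which allows for patients who have not yet consented to use DIABEO.

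Other points also stand. Adverse events are reported throughout with no arm limit, so severe hypoglycaemia in continuing controls might be captured that way, though the article does not say so and it is not the dedicated assessment used at months 6 and 12. Comparing groups at month 24 can legitimately mean arm 2 against arm 3 (although these sit in different regions) or early against delayed start. The detailed handling of switchers may sit in a full protocol or SAP that is not shown, and its absence is not counted here.

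What the reply does not remove is the conflict between Table 1 and the outcome list for two outcomes, or the fact that the month-24 contrast is no longer against protected usual care while nothing in the article says so.

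**Conclusion.** The point holds in a limited form. For severe hypoglycaemia and EQ-5D, and so for the 24-month cost per severe hypoglycaemia avoided, the article plans a comparison of groups while Table 1 sets the month-24 assessment for groups 2 and 3 only. That is a contradiction on the page. For HbA1c, responders and costs, a month-24 control group may well exist, but it is neither protected nor guaranteed to be on usual care, and any intention-to-treat contrast is diluted by an unknown share.

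The dilution figures rest on three assumptions: the 0.5-point effect persists, switchers gain it in full, and x takes the values tried. They show direction and possible scale and do not predict the result.

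The primary outcome and the sample size are both set at 12 months, before controls may start the software, and all affected outcomes are secondary. This is a moderate issue of labelling and consistency, not one that must be fixed before the trial can be relied on.

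**What to change.** 1. In Outcome Measures, limit the randomised comparisons with usual follow-up to time points up to month 12. Apply the same limit to costs and cost-effectiveness ratios, including cost per severe hypoglycaemia avoided.
2. Reconcile Outcome Measures with Table 1 for month-24 severe hypoglycaemia and EQ-5D, so that both name the same arms. Correct the Visit 4 header notes at the same time.
3. Keep month 24, but label it as descriptive: early against optional delayed start by randomised group, with switchers also shown separately, and durability within arms 2 and 3. An arm 2 against arm 3 summary can stay on the same footing, with the regional difference noted. Deleting every 24-month group summary is unnecessary.

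The cost is a change of wording and the loss of a nominal 24-month controlled claim that the design does not secure. Adding control assessments at month 24 instead is probably no longer practical: inclusion ended on 19 May 2016, so the last patients would reach month 24 in May 2018, just before the primary completion expected in June 2018.

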### Statistical Analysis

#### Patient Population Size

The initial sample size to detect a ≥0.5% difference in HbA_1c_ from baseline to month 12 was estimated using a standard deviation of 1.2%, a rate of not evaluable patients of 15% and an intracluster correlation coefficient of .005 (a measure degree of homogeneity within the same region). This calculation predicted an initial sample size of 696 patients to achieve ≥90% power in detecting a difference in outcome.

#### Data Analysis

Efficacy outcomes are analyzed on an intention-to-treat basis. A confirmatory analysis adjusted by center and region will be carried out and a robustness analysis will be done on the population per protocol. Categorical data are expressed as frequencies and percentages, while quantitative data are expressed as means and standard deviations. The analysis of covariance (ANCOVA) is used to compare groups for the results on the primary end point. The ANCOVA, the chi-square test, and Fisher exact test are used for other comparisons.

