### Inclusion Criteria

Patients enrolled in the TELESAGE study should meet the following inclusion criteria: T1DM and T2DM patient performing self-monitoring of blood glucose (≥2 measured values per day), treated with insulin analogs according to a basal-bolus regimen for at least 1 year and using the same method of administration (pen or pump) for at least 3 months, possessing an Apple or Android smartphone compatible with DIABEO before starting the study, having two HbA_1c_ values ≥8%, one dating to more than 3 months ago and the other less than 1 month ago. Additionally, participants must have the capability to understand and follow the instructions of the study, and be able to provide written consent to participate and specify if they benefit from a social security scheme.

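### No stated analysis of the responder rate uses baseline HbA1c; the unadjusted test is valid but gives up modest precision on this secondary outcome

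*Protocol article*

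**What the plan says.** The Outcome Measures section lists among the secondary outcomes, at 6, 12 and 24 months, the "percent of responder patients (HbA_1c_ <7.5% or HbA_1c_ reduction ≥1" percent). The Data Analysis section says of the primary end point: "The analysis of covariance (ANCOVA) is used to compare groups for the results on the primary end point". For everything else it says: "The ANCOVA, the chi-square test, and Fisher exact test are used for other comparisons". It does not pair tests with outcomes, but chi-square and Fisher are the only ones listed that apply to a yes/no outcome. One adjusted analysis is described: "A confirmatory analysis adjusted by center and region will be carried out". Baseline HbA1c is not among its stated adjusters.

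A baseline value exists for everyone. Entry requires "having two HbA_1c_ values ≥8%, one dating to more than 3 months ago and the other less than 1 month ago", and Table 1 records HbA1c at the first visit.

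**The concern.** Responder status is computed from baseline and follow-up HbA1c, so it may well be related to baseline. Chi-square and Fisher tests cannot use a continuous covariate. If the relation exists, two things follow. The risk difference has a wider confidence interval than the data allow. And a chance difference in baseline HbA1c between arms moves the responder comparison, with nothing in the stated analysis to take it out. The continuous end point is analysed by ANCOVA, so two readings of the same HbA1c data would be handled with unequal efficiency.

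**Working it through.** **Arm sizes from the plan's own figure.** The article gives no power for the responder outcome; its stated figure is the total of 696. The inputs are a difference of 0.5 ("The initial sample size to detect a ≥0.5% difference in HbA_1c_ from baseline to month 12"), "a standard deviation of 1.2%, a rate of not evaluable patients of 15% and an intracluster correlation coefficient of .005", and at least 90% power. Alpha is not stated. With two-sided alpha 0.05/3 and three equal arms:

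- n per arm = 2 × (1.2/0.5)² × (2.394 + 1.282)² ≈ 156, so 3 × 156 = 468 evaluable.
- 468/0.85 = 550.6 enrolled before clustering.
- Design effect 1 + (m − 1) × 0.005. With 12 regions, m = 696/12 = 58 enrolled or 58 × 0.85 = 49.3 evaluable, giving 1.285 or 1.2415.
- Total 550.6 × 1.2415 ≈ 684 to 550.6 × 1.285 ≈ 708.

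This brackets 696. Other choices of alpha and clustering also come close, so the alpha used cannot be identified. With 1:2 allocation the arms are about 232 each, or 232 × 0.85 ≈ 197 evaluable. Within one set of six regions the comparison is about 116 v 232, or 99 v 197 evaluable. Both pairings are shown below.

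**What the rule itself does.** The fall needed is min(baseline − 7.5, 1.0): just over 0.5 at 8.0%, just over 0.7 at 8.2%, and 1.0 from 8.5% upward. The built-in dependence is confined to 8.0–8.5%, where it makes response easier. Above that, dependence on baseline comes only from regression to the mean, which makes response more frequent at high baseline.

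**Simulation 1: how the gain depends on regression to the mean.** Assumed, not in the article: mean baseline 9.1%, baseline SD 0.8–1.2, control drift −0.2, two-sided alpha 0.05, no clustering. The plan's 1.2 is read as the SD of change, and the true effect is the plan's 0.5. Chi-square is compared with logistic regression on arm and baseline (5,000 runs; 3,000 under the null). The slope is that of month-12 HbA1c on baseline; 1.0 means no regression to the mean.

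| Slope | Power, 99 v 197: chi-square → adjusted | Gain, 99 v 197 | Gain, 197 v 197 |
|---|---|---|---|
| 0.3 | 74–79% → 79–89% | 5–10 points | 4–5 points |
| 0.5 | 74–76% → 77–81% | 2–4 | 1–3 |
| 0.7 | 74–76% → 74–76% | under 1 | 0–1 |
| 1.0 | no gain | 0 | about 0 |

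The odds ratio of response per baseline point runs from about 0.9 (slope 1.0) through 1.4 and 1.9 to 2.7–3.4 (slope 0.3). Type I error is near 5% for both tests throughout.

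**Simulation 2: selection on two values of at least 8%, as the entry criteria require.** Assumed pre-study mean 8.5%. Two settings give an SD of change near 1.2: pre-study SD 1.6 with a baseline to month-12 correlation of 0.70 (slope 0.65), and SD 1.3 with correlation 0.50 (slope 0.46). Adjustment is for baseline with a bend at 8.5%. With no treatment effect, response rises from about 18% at baseline 8.0–8.4% to 41–53% at 10% or more.

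| Comparison | True effect | Power, setting 1 | Power, setting 2 |
|---|---|---|---|
| 99 v 197 | 0.5 | 75% → 79% | 75% → 80% |
| 99 v 197 | 0.35 | 45% → 50% | 43% → 48% |
| 197 v 197 | 0.5 | 90% → 91% | 90% → 93% |

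The variance ratio, adjusted to unadjusted, is about 0.91–0.95, and the mean risk difference is unchanged. A repeat run gave 73–75% → 79–80% for the first row. In one run the robust standard error rejected slightly too often under the null (5.2–6.4%, against 4.9–5.4% unadjusted), so the variance ratio is the cleaner measure.

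**Chance imbalance.** The SD of the baseline difference at 99 v 197 is SD × √(1/99 + 1/197) = SD × 0.123, or about 0.10 to 0.15 for SD 0.8 to 1.2. In simulation 1, an imbalance of 0.2 shifts the unadjusted risk difference by about 4, 2.5, 1.5 and −0.4 percentage points at slopes 0.3, 0.5, 0.7 and 1.0, against a true difference of about 15.

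**The case against.** The unadjusted comparison is valid: its type I error is about 5%, its risk difference is right on average, and chance imbalance is already covered by its error rate. The outcome is secondary, and the trial is sized on the HbA1c difference, which ANCOVA handles. A journal article need not list every covariate, and the Data Analysis section neither assigns a test to each outcome nor confines itself to unadjusted analyses. All of this stands, and it limits the point to efficiency. It does not remove it: the article does name its tests, those that fit a binary outcome are unadjusted, and the confirmatory analysis names its adjusters without baseline HbA1c.

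A reader might infer that response depends strongly on baseline because of how the rule is built. The documents do not support that. They give no baseline SD, correlation or responder rate. The rule varies with baseline only between 8.0% and 8.5%, and there it works against regression to the mean. The strength of dependence ranges from none to marked according to the regression assumed. A reader might also infer that the planned test is biased or the responder result unreliable; the calculations show neither.

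**Conclusion.** The point holds as a minor, free improvement on a secondary outcome. No stated analysis of the responder rate uses baseline HbA1c. Under inputs that match the plan's SD of 1.2 with moderate regression to the mean, adjustment cuts the variance of the risk difference by about 5–9% and adds about 1–6 points of power, the larger gains being at 99 v 197. Stronger regression would give more, and with little or none the gain is nil. These sizes rest on the assumed baseline distribution, slope and drift, none of which the article states. Selection on two high values makes some regression to the mean likely, but its amount is not known from the documents.

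**What to change.** In the Data Analysis section, and in the analysis plan if it follows the same wording:

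- Analyse the responder rate by logistic regression on arm and continuous baseline HbA1c, allowing a bend at 8.5%, where the rule changes.
- Report the standardised (marginal) risk difference versus arm 1 with its confidence interval. This keeps the same target as the raw difference in percentages.
- Include baseline HbA1c in the center- and region-adjusted confirmatory analysis of this outcome.
- Keep the chi-square or Fisher test as a supportive check.

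The cost is a sentence or two of wording, fixed before the data are analysed. No new data, visits or patients are needed.
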